### 2.2 Primary and secondary endpoints

#### *Primary endpoints*

- I. Oswestry disability index (ODI)
- II. Dynamic compensation

#### *Secondary endpoints*

- III. Sagittal spinal alignment and spinal loads assessed using motion capture
- IV. Sagittal spinal alignment assessed using EOS
- V. Sagittal spinal alignment assessed using the optically captured 3D back surface (Artec EVA)
- VI. Muscle fatigue
  1. assessed using electromyography (EMG)
  2. fatigue exercise duration
- VII. Radiological parameters
  1. Muscle atrophy
  2. Fatty infiltration
  3. Muscle cross-sectional area

4. Stenosis severity
5. Segmental instability

#### Other parameters

- VIII. Quality of life (EQ-5D-5L)
- IX. Swiss spinal stenosis score
- X. Tampa scale of kinesiophobia
- XI. Core Outcome Measures Index for the back (COMI back)
- XII. Upper body motion (inertial sensor data)
- XIII. Manual testing for muscle strength
- XIV. Physical activity level
- XV. Back performance scale
- XVI. Surgical information
  1. Scheduled decompression surgery
  2. Scheduled fusion of vertebrae
  3. Number of decompressed levels
  4. Number of instrumented levels
  5. In case of instrumentation:
    - Fusion with Cage
    - Fusion without Cage
- XVII. ICHOM
  1. Age
  2. Sex
  3. Body mass
  4. Body height
  5. Body mass index (BMI)
  6. Pain medication
  7. Previous treatment (physiotherapy, infiltration, other)
  8. Own physical exercise program
  9. Education, occupation, level of permanent invalidity, social situation, need of care
  10. Duration of symptoms categorized as <1 year, 2–5 years, and >5 years

## 2.3 Project design

This study is designed as a single-center, longitudinal observational study. For each patient, a multimodal set of data including experimental, clinical, functional, radiological and biomechanical data is compiled before and after routine surgical intervention. There will be two study visits: baseline and one-year follow-up (Figure 1).

[figure not shown]

### **3. PROJECT POPULATION AND STUDY PROCEDURES**

#### **3.1 Project population, inclusion and exclusion criteria**

We plan to include 122 patients with sLSS (61 per year) in this study, which will be realistic and sufficient for the proposed statistical analysis (see Section 4.1). Patients will be recruited at the Department of Spine Surgery at the University Hospital Basel. The surgical procedure is not affected by the study and is not subject of investigation. All patients will receive – depending on their clinical and imaging diagnostics – lumbar decompression alone or decompression combined with fusion either through posterolateral fusion with pedicle screw-rod system with autologous bone apposition or through transforaminal lumbar interbody fusion with a cage filled with autologous bone implanted from posterolateral into the intervertebral space. Decompression will be performed as either open surgery or microsurgical technique, and both are performed through a midline approach. The open surgery decompression will be performed via an interspinous approach with interlaminar flavectomy, whereas in the microsurgical technique, uni- or bilateral fenestration and flavectomy will be performed.

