#### Secondary hypotheses

Hypothesis 2.1: PROMs correlate more strongly with quantitative functional parameters including muscle fatigue, spinal load and biomechanical parameters or lumbopelvic range of motion during forward trunk bending and during walking than with pathomorphological parameters including severity of stenosis, segmental instability and muscle degeneration.

Hypothesis 2.2: Changes in PROMs correlate with changes in static and dynamic spinal imbalance, muscle fatigue and extent of forward trunk bending, lumbopelvic range of motion during walking and spinal loads from before to after spinal stenosis surgery.

Hypothesis 2.3: Patients with sLSS with greater muscle degeneration and greater spinal imbalance have greater muscle fatigue.

Hypothesis 2.4: At follow-up, patients with spinal stenosis will have improved PROMs, less static and dynamic spinal imbalance and muscle fatigue, and less forward trunk bending and larger lumbopelvic range of motion during walking than before spinal stenosis surgery.

Hypothesis 2.5: Postoperative PROMs are explained by preoperative severity of LSS, spinal alignment, segmental instability, muscle degeneration, dynamic compensation, muscle fatigue and spinal load.

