### III. Sagittal spinal balance and spinal loads assessed using motion capture

The curvature of the lumbar and thoracic spine during stance and during walking will be computed from the marker data using MATLAB™ (R2021b, The Mathworks Inc., Massachusetts, USA) software. A cubic polynomial function will be fitted to the marker positions in each time frame, approximating an S-shaped spine curvature with thoracic kyphosis (TK) and lumbar lordosis (LL) curves [1]. The workflow used to calculate sagittal spinal balance parameters is based on the calculation methods for radiological sagittal spinal balance parameters and was established and tested in a previously conducted pilot study (EKNZ Project ID 2021-02012). The set of marker-based sagittal spinal balance parameters comprises LL, TK, sagittal vertical axis (SVA), spino-sacral angle (SSA), spine inclination (SI) (Figure 3).

[figure not shown]

**Figure 3:** Computed Marker Data and Calculation of Sagittal Spinal Balance Parameters [1]

The data obtained using motion capture will be used to estimate spinal load using musculoskeletal modeling [28].

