## 4 STATISTICS AND METHODOLOGY

### 4.1 Sample size calculation

To determine if PROMs correlate with dynamic compensation considering categorical covariates with 3 levels of the covariate a sample size of 111 (37 within each level) is required to detect a correlation of 0.3 at 80% power and 5% significance level. Considering a 10% drop-out rate, 122 subjects will be enrolled in the study.

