violation of this assumption in the data we will use more appropriate statistical methods (e.g., nonparametric methods). Our predictive model building approach will be based on the seven steps of Steyerberg's [45] to construct a predictive model to predict the surgical outcome from preoperative clinical, functional, radiological, and biomechanical data and musculoskeletal model prediction of postoperative local spinal loads. Data will be checked for accuracy, inconsistencies, and plausibility of the recorded information in the data, and if required re-coding/re-grouping of certain variables will be done. We will restrict categorizing the continuous variables in the model development stage as much as possible to avoid loss of information and assess the predictive ability of the clinically relevant variables (e.g., from preoperative – spinal alignment, segmental instability, muscle degeneration, dynamic compensation, muscle fatigue, and biomechanical parameters) and variables with good/high predictive performance will be used to construct the predictive models. A different set of predictive models will be set up using the candidate predictors with the outcome PROMs. We will compare the predictive performance of the models to select the best-performed model using appropriate statistical methods (e.g., R^2). The predictive models will be based on collected experimental data and also simulated data. As a few of the highly clinically relevant variables cannot be measured directly we will use the experimental data to simulate these variables. For the internal validation of the selected predictive model, we will use cross-validation.

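### Section 3.1 calls 122 patients sufficient for the whole planned analysis, but Section 4.1 sizes only Hypothesis 1; adequacy for the Hypothesis 2.5 prediction model is not shown and needs few parameters and a high R²

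*Protocol*

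**What the plan says.** Section 3.1 justifies the planned enrolment of 122 as "which will be realistic and sufficient for the proposed statistical analysis (see Section 4.1". The statement covers the proposed analysis as a whole and names its own support.

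That support, Section 4.1, opens with "To determine if PROMs correlate with dynamic compensation considering categorical covariates with 3 levels of the covariate" and continues "a sample size of 111 (37 within each level) is required to detect a correlation of 0.3 at 80% power and 5% significance level". It ends with "Considering a 10% drop-out rate, 122 subjects will be enrolled in the study". No other hypothesis is given a size or a precision.

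Hypothesis 2.5 (Section 2.1) reads "Postoperative PROMs are explained by preoperative severity of LSS, spinal alignment, segmental instability, muscle degeneration, dynamic compensation, muscle fatigue and spinal load". That is seven domains. Some have several measures; for motion-capture alignment, Section 3.3 (III) says "The set of marker-based sagittal spinal balance parameters comprises LL, TK, sagittal vertical axis (SVA), spino-sacral angle (SSA), spine inclination (SI".

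Section 4.2 describes the model building. Candidates are assessed for predictive ability, and "variables with good/high predictive performance will be used to construct the predictive models". Then "A different set of predictive models will be set up using the candidate predictors with the outcome PROMs"; the best performer is chosen, with R² given as an example criterion. Cross-validation is then planned as internal validation of the model selected. The number of candidates, the number of models and the expected R² are not given.

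**The concern.** A calculation for one correlation says nothing about how many parameters a prediction model can carry. If a model has too many parameters for its data, or its variables are chosen for performance in those same data, the coefficients are too large and the apparent R² is too high. If validation starts only after that choice, the validated R² can inherit part of the optimism.

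Hypothesis 2.5 is secondary, but the protocol puts weight on it: the background (Section 1) expects the results to guide treatment at the clinic and to help predict the outcome of therapies. A reader who takes Section 3.1 at face value would think the sample had been shown adequate for that purpose.

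**Working it through.** **1. The plan's own figure.** For a two-sided 5% test of r = 0.3 at 80% power (two-sided is assumed; the protocol does not say), Fisher's z gives n = ((1.960 + 0.842)/atanh 0.3)² + 3 = (2.802/0.3095)² + 3 = 84.9, so 85. It is 87 with adjustment for a three-level covariate and 91 with three strata. The stated 111 is not reproduced but is larger; it gives about 88 to 90% power for the association over all patients. So Section 4.1 does support Hypothesis 1 on that reading. How 111 was obtained is a separate question.

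**2. Patients available for Hypothesis 2.5.** It needs one-year PROMs: 122 × 0.9 = 109.8, so about 109 to 110.

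**3. Parameters.** Seven is the floor, with one per domain. The measures defined in Section 3.3 allow more:

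- alignment: 5 marker-based parameters
- dynamic compensation: a static-minus-dynamic difference, so up to 5
- muscle degeneration: three averaged areas on each side, so 6
- fatigue: 2
- stenosis severity, instability and load: at least 1 each

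The sum is 5 + 5 + 6 + 2 + 3 = 21, or 25 with the four EOS alignment parameters. This is a count of what is measured, not a number the protocol commits to.

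**4. Size needed for shrinkage S = 0.9.** Both S and R² are assumptions. With p parameters, n = p / ((S − 1) · ln(1 − R²/S)). Example, p = 7 and R² = 0.30: ln(1 − 0.3333) = −0.4055, and 7/(0.1 × 0.4055) = 172.6, so 173.

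| Assumed R² | n for p = 7 | Most parameters that 109 supports |
|---|---|---|
| 0.2 | 279 | 2 (needs 80; 3 need 120) |
| 0.3 | 173 | 4 (needs 99; 5 need 124) |
| 0.4 | 120 | 6 (needs 103; 7 need 120) |
| 0.5 | 87 | 8 (needs 99; 9 need 111) |

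With p = 20 and R² = 0.30, n = 494. Setting n = 109 and p = 7 and solving for R² gives 0.9 × (1 − exp(−7/10.9)) = 0.43, the break-even value for one parameter per domain.

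**5. Expected shrinkage at n = 109, R² = 0.30.** The same equation solved for S gives 0.85 for p = 7 (check: 7/(0.148 × 0.434) = 109) and 0.68 for p = 20 (check: 20/(0.317 × 0.578) = 109). A route through adjusted R² at n = 110 gives the same two values. At p = 7 it gives 0.78 for R² = 0.2 and 0.92 for R² = 0.5.

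**6. Order of selection and validation.** Simulation with 110 patients, 21 candidates of which 7 truly predict, true R² 0.30, and univariable screening at p < 0.05. All of these are assumptions. Mean R²:

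| Predictor correlation | Apparent | Cross-validated after selection | Selection repeated in each fold | New data |
|---|---|---|---|---|
| 0 | 0.30 | 0.22 | 0.10 | 0.13 |
| 0.3 | 0.40 | 0.11 | 0.16 | 0.17 |

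Cross-validating only the selected model was too optimistic in the first case and too pessimistic in the second. Repeating selection inside the folds was closer to new-data performance in both.

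**The case against.** Sizing a study on its primary hypothesis is normal. Section 3.1 sends the reader to Section 4.1, which says openly what it sizes, and Hypothesis 2.5 is secondary. Section 4.2 also has safeguards: cross-validation, a published stepwise modelling framework and restraint in categorising continuous variables. The candidate list and any penalty may properly sit in a statistical analysis plan that is not at hand, so their absence is not a fault. All of this stands. What it does not answer is that the protocol itself claims sufficiency for more than its cited calculation covers, and itself describes selection before validation.

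A reader might infer three stronger things:

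- *The model will be heavily overfitted.* The protocol gives neither the candidate count nor an R², so this does not follow. With seven parameters and R² of 0.3 to 0.5, shrinkage is 0.85 to 0.92, which is mild.
- *Shrinkage at 109 is only 0.82 (7 parameters) or 0.49 (20).* These come from 1 − p/(−109 · ln(1 − 0.30)), which treats 0.30 as the apparent R², whereas the sample-size formula treats it as the optimism-corrected value. Used consistently, the results are 0.85 and 0.68.
- *The validated R² must be too high.* The simulation shows that its direction depends on how the predictors are correlated. The defensible statement is that it can be biased.

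**Conclusion.** The point holds in a limited form. Sufficiency is shown for Hypothesis 1 only. For the Hypothesis 2.5 model it is not shown, and against a shrinkage target of 0.9 it fails unless few parameters are used and R² is high: seven parameters need an R² of about 0.43 or more at 109 completers. Overfitting would be mild with one variable per domain and substantial with about 20 or more candidates, a number the listed measures could reach but the protocol does not state. The planned cross-validation can reveal optimism, but it does not make the sample adequate, and in the order written its result can be biased.

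These sizes rest on an assumed R² (0.2 to 0.5), the 0.9 target, 10% dropout and, for the validation point, the simulated settings. The mismatch between Sections 3.1 and 4.1 rests on no assumption. The primary analysis is not affected; this should be corrected but does not threaten the study.

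**What to change.** **Section 3.1:** limit the statement to Hypothesis 1 by saying that the sample size is based on the primary hypothesis and that the prediction model for Hypothesis 2.5 is exploratory.

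**Section 4.2:** state that variable screening and the choice among models are repeated inside every cross-validation fold, and report the R² from that procedure. Limit the candidates to a small prespecified set, for example one variable per Hypothesis 2.5 domain. Because seven unpenalised parameters still miss the 0.9 target at R² = 0.30 (173 needed), shrinkage such as ridge or elastic net is a sensible option, tuned within the folds; it is one choice among several.

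**Cost:** a few sentences, no additional patients or measurements, and slightly more analysis work. The reported R² will probably look less favourable, and measures outside the prespecified set would not be candidates for this model.

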##### *Inclusion criteria:*

- age > 30 years
- BMI < 35 kg/m^2
- diagnosed sLSS
- clinical symptoms for at least 6 months
- intermittent neurogenic claudication with limitations of their walking ability due to symptoms in the lower back and or in one or both legs
- unsuccessful conservative treatment
- confirmation of the LSS through MRI
- scheduled for surgery

##### *Exclusion criteria*

- inability to provide informed consent
- previous spine surgery
- use of walking aids
- other neurologic disorders affecting gait
- MRI incompatibility
- pregnancy

#### **3.2 Recruitment, screening and informed consent procedure**

Patients with sLSS will be recruited at the Clinic for Spine Surgery at the University Hospital Basel (Switzerland). Clinical treatment will not be affected by the study. Patients will be informed about the study at the time of indicating for surgery. In addition, patients will be screened using the hospital's surgery schedule tool. Patients with sLSS scheduled for decompression surgery will be selected by the PhD student and/or trained members of the research group. Medical history, inclusion and exclusion criteria of the screened patients will be checked by the study physician. Eligible patients will be contacted and informed about the study. Inclusion- and exclusion criteria will be checked again during the call and at the time of consent.

#### **3.3 Study procedures**

After the patients' arrival at the movement laboratory, the patient is informed in detail about all study procedures. If there are no questions from the patient, the informed consent form is signed. Subsequently, clinical and demographic parameters including age, body mass, body height, pain medication, previous treatment (physiotherapy, infiltration, other), duration of symptoms and own physical exercise program will be recorded on the case report file. In a next step, participants will

be asked to complete several PROMs questionnaires including the validated German versions of the ODI, EQ-5D-5L, Swiss Spinal Stenosis Questionnaire, Tampa scale of kinesiophobia and Spine Tango COMI. PROMs will be digitally collected using iPads and surveys created on the REDCap® [22] web application for building and managing online surveys and databases (approximate duration: 15 minutes).

After completion of the questionnaires, all participants will be prepared for the functional biomechanical analysis, which starts with a clinical measurement of the active and passive range of motion of ankle, knee and hip joints. This also includes a neurological examination of the key muscles according to Janda, and a test used to elicit Trendelenburg signs. Next, the back performance scale movement assessment will be performed. The assessment includes five separate tests (Sock Test, Pick-up Test, Roll-up Test, Fingertip-to-Floor Test, and Lift Test) that will only be performed if allowed by the patients' current pain situation (approximate duration: 30 minutes).

Prior to placement of surface EMG electrodes, specific skin areas will be shaved and cleaned, if necessary. Electrodes will be placed on selected abdominal and paraspinal muscles. Reflective markers will be placed on anatomical landmarks (approximate duration: 45 minutes).

Participants will complete forward-bending, pick-up, trunk torsion, sitting and walking assessments before and after a fatigue exercise. Paraspinal muscle fatigue will be elicited by a modified Biering-Sørensen test [23] on a Roman chair (45° chair inclination, trunk horizontal). The modified Biering-Sørensen test will be conducted immediately before the movement assessments will be repeated to obtain data in the fatigued state. At the very end of the movement analysis, patients will complete the sock test from the back performance scale assessment again with the retroreflective markers attached (approximate duration: 30 minutes).

After the functional biomechanical analysis, radiological data (MRI and EOS) will be collected. MR imaging of the lumbar and abdomen region will be performed using a 0.55T MAGNETOM Free.max scanner (Siemens Healthcare, Erlangen, Germany) with the patients in supine position with extended legs. MR imaging allows the classification of level and severity of stenosis. Patients' back surfaces and markers will be digitized using the contactless optical scanner Artec EVA [24]. This procedure will be performed in the laboratory facilities at the University Hospital of Basel, same as in the previous study approved by the EKNZ (Project ID: 2020-02496 dated 11/12/2020). This procedure does not require any additional preparation of the participant, but their pose will be referenced with a pose frame replicating the standing posture from the EOS radiography (approximate duration: 5–7 minutes). Multi-echo gradient echo (VIBE Dixon) axial images will be acquired for the analysis of the abdominal and paraspinal muscles. A T2-weighted axial image will be selected at each vertebral body level in the center of the body itself identified on the sagittal view image. All sequences are not enhanced (approximate duration: 30 minutes). Finally, upright standing sagittal plane EOS images of the full body including entire spine and pelvis will be captured (approximate duration: 10 minutes). The total duration of the baseline study visit on test day 1 including travel times between facilities will be approximately 3.5 hours. Because baseline and 1-year follow-up entail the same study procedures, a complete study participation will take approximately 7 hours.

Participants will be handed out activity monitors after test-day one and test-day two. The same activity monitor will be sent to study participants six months after the spine surgery. Participants will be asked to wear the activity monitor for nine days on their wrist. Participants will be given prepaid envelopes to return the devices. In addition, participants will be asked to complete a digital set of PROMs six months after the spine surgery sent to them via e-mail. If no e-mail address is available, printed versions will be sent together with the activity monitor.

## **Movement data collection and processing**

Biomechanical parameters will be recorded with 120 Hz using a 3-dimensional motion capture system with 10 infrared cameras (Vicon Vero 2.2, Vicon Motion Systems Ltd, Oxford, UK). The marker set will consist of 71 reflective skin markers, including a full-body marker set (53 markers) based on the Conventional Gait Model (CGM) 2.3 [25], enhanced by a self-induced detailed trunk/spine marker set with 19 markers applied over the spinous processes of the following

vertebrae: C7, T1, T2, T3, T4, T5, T6, T7, T8, T9, T10, T11, T12, L1, L2, L3, L4, L5 and S1 (Figure 2). The CGM 2.3 requires the measurement of anthropometrical parameters including leg length, knee width, malleolar-width, shoulder offset, elbow width, wrist width and hand thickness.

Patients will wear their normal comfortable flat shoes. Spatio-temporal and kinematic data will be recorded for all movement assessments and gait trials. For the measurement of the static spinal alignment, participants will be instructed to stand in a natural upright posture with their feet hip-wide apart, arms hanging relaxed at the sides. For the forward-bending assessment, patients will be instructed to stand in a natural upright posture with their feet hip-wide apart, arms hanging relaxed at the sides, and slowly bend forward at a self-selected speed until the end of range of motion is achieved and then return to the upright position, while keeping their knees extended during the entire task. For the pick-up assessment, patients are asked to grab and lift an object from the ground and place it on a table (height: 76cm). During the trunk-torsion assessment, patients are asked to grab an object (empty card board box) and move it from one side of the table to the other side with extended arms without moving their feet. Next, data are captured in a sequence during which the patient is asked to sit down on a chair, relax for a few seconds and stand up again. Then, patients will walk back and forth across the walkway at their preferred walking speed.

During the fatigue exercise, paraspinal muscle fatigue will be elicited by a modified Biering-Sørensen test [23] on a Roman chair (45° chair inclination, trunk horizontal). The test is only conducted within tolerable pain levels until the participant terminates the exercise by choosing to support the torso with hands and arms on a cushion placed below the trunk. The duration of the fatigue exercise from start until termination will be measured.

[figure not shown]

**Figure 2:** Dorsal Marker Placement

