## VI. Muscle fatigue

Muscle fatigue will be quantified using two parameters. First, the fatigue exercise duration will be measured using a stopwatch. Time is stopped from the point where the patients starts the exercise by no longer supporting the torso with their hands until the termination of the exercise by supporting the torso. Second, muscle fatigue will be assessed as the decrease in median EMG frequency as described by Boutellier et al. (2021) [31].

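### The back-extension hold may end because of pain, yet its duration is scored as muscle fatigue and no stop reason is requested; on that measure, pain relief after surgery could read as less fatigue

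*Protocol*

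**What the plan says.** Protocol section 3.3 (Movement data collection and processing) describes the fatigue exercise, a modified Biering-Sørensen hold on a Roman chair. Its stopping rule is: "The test is only conducted within tolerable pain levels until the participant terminates the exercise by choosing to support the torso". What is recorded is: "The duration of the fatigue exercise from start until termination will be measured".

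Under Assessment of study parameters, item VI, the protocol states: "Muscle fatigue will be quantified using two parameters. First, the fatigue exercise duration will be measured using a stopwatch". The second parameter is the fall in median EMG frequency. Section 2.2 lists "fatigue exercise duration" as a secondary endpoint in its own right, beside the EMG measure.

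The exercise is done at baseline and at one year. Hypothesis 2.4 expects that at follow-up "patients with spinal stenosis will have improved PROMs, less static and dynamic spinal imbalance and muscle fatigue". Hypothesis 2.2 links changes in PROMs to changes in muscle fatigue, among other variables. Section 4.2 assigns a paired t-test to the pre- to postoperative difference and a correlation of differences to the association of changes.

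**The concern.** One stopwatch value can have two causes: the back muscles are exhausted, or pain has passed what the patient tolerates. Both are scored as muscle fatigue. If surgery relieves pain, some patients may hold longer a year later with unchanged muscles. On duration, that would count as support for Hypothesis 2.4. The same pain relief would move PROMs and duration together, which adds to the correlation examined under Hypothesis 2.2. In both cases the error lies in the direction the study hopes to find.

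The missing item is a matter of data collection. A statistical analysis plan can specify adjusted or sensitivity analyses, but it cannot recover a stop reason that nobody wrote down.

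**Working it through.** **1. Is the cause of stopping recorded anywhere visible?** The text defining the exercise and the text defining the endpoint ask only for time. Section 3.3 lists the clinical and demographic items for the case report form, and a stop reason is not among them. Pain and symptoms are collected at the visit through the EQ-5D-5L pain dimension, symptom intensity in the Swiss Spinal Stenosis Questionnaire, and pain medication; the Tampa scale covers fear of movement. The order matters, however: "After completion of the questionnaires, all participants will be prepared for the functional biomechanical analysis". By the protocol's approximate timings, the clinical tests (30 minutes) and marker and electrode placement (45 minutes) come between the questionnaires and the movement session. That is 30 + 45 = 75 minutes, followed by the unfatigued movement tasks, before the hold begins. A questionnaire score can describe the patient's pain that day. It cannot show what ended the hold.

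**2. Size: nothing to reproduce.** The protocol gives no figure for hold time or pain stops, so everything in steps 3 and 4 illustrates with assumed inputs.

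**3. Closed form for Hypothesis 2.4.** The only document input is the number of completers: 122 × 0.9 = 109.8, taken as 110. Assumed: coefficient of variation of hold time 0.5, test-retest correlation 0.7, no true change in the muscle, pain stops unrelated to fatigability.

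- Standard error of the mean change = 0.5 × √(2 × (1 − 0.7)) / √110 = 3.7% of mean hold time.
- Net shift = (share stopped by pain before − share after) × (1 − fraction of own limit reached).
- Chance of falsely declaring longer holds = Φ(shift/SE − 1.96), nominal 2.5%.

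For example, with 20% stopped by pain before and 5% after, at 70% of their own limit, the shift is 0.15 × 0.30 = 4.5%, and Φ(4.5/3.7 − 1.96) is about 0.23. A shift of 1.2% gives 5%, and 7.2% gives 50%.

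Simulation with log-normal hold times, 8,000 studies per setting, agrees:

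| Stopped by pain, before / after | at 90% of own limit | at 70% | at 50% |
|---|---|---|---|
| 0 / 0 | 2.5% | 2.4% | 2.4% |
| 10% / 5% | 3.6% | 6.1% | 10.1% |
| 20% / 15% | 3.4% | 6.3% | 9.4% |
| 20% / 5% | 5.7% | 22.0% | 46.0% |
| 40% / 10% | 13.1% | 66.5% | 95.4% |

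**4. A second model.** Here observed time is the smaller of a fatigue limit (median 90 s, unchanged by surgery) and a pain limit, with n = 111. Median pain limits of 150, 90 and 60 s make pain end about 26%, 50% and 69% of baseline holds.

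- If surgery raises the median pain limit by 25%, mean duration rises by about 3, 6 and 8 s, and a significant increase appears in 24%, 77% and 97% of runs.
- With no median change in the pain limit, the figure is at most 2%.
- In the 25% case, the change in duration correlates 0.31 to 0.62 with the change in pain limit. If PROM change correlates 0.5 to 0.7 with that change and has no other link to duration, the correlation relevant to Hypothesis 2.2 is 0.31 × 0.5 = 0.16 to 0.62 × 0.7 = 0.43. The study is sized for 0.3.

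Both models give the same direction when pain is relieved. Neither establishes a size.

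**5. What a stop reason would buy.** In the 20% / 5% setting, at 70% and 50% of the limit, restricting to patients with no pain stop at either visit returns the false rate to 2.5-2.6%. It is 5.9-9.3% if 30% of pain stops are misreported. This rests on the assumption that pain stops are unrelated to fatigability.

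**The case against.** The strongest objection is that pain stops may be rare. A reader might infer that they are common from the entry criterion of "limitations of their walking ability due to symptoms in the lower back and or in one or both legs". But that criterion concerns walking. The protocol's background says symptoms worsen with standing and walking and ease with sitting, lying or forward bending, and the hold is neither upright standing nor walking. A loaded back extension can still hurt, and the protocol found a pain limit necessary for this test. But no passage shows that pain ends a meaningful share of holds, so the lower rows of the table cannot be presented as expected values.

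A reader might also infer that pain is not measured at all, or that the whole fatigue endpoint is compromised. Neither follows. Visit-level pain and symptoms are collected and allow some adjustment. EMG is a separate listed parameter that nothing in the documents shows to be affected, and a longer hold without a matching EMG change would be visible.

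Hypothesis 2.1 is also a tempting target: "PROMs correlate more strongly with quantitative functional parameters including muscle fatigue". There, fatigue is treated as a functional parameter and set against pathomorphology. A pain-limited hold is still a real functional finding, so for that comparison the dispute is largely about the label.

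Finally, the case report form is not shown and may hold a stop field. That stands as a limit. The point is only that the protocol text defining the measure does not ask for one.

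**Conclusion.** The point holds for the duration measure only. As written, the plan cannot separate a hold ended by exhaustion from one ended by pain. Pain relief could therefore read as less muscle fatigue under Hypothesis 2.4 and add to the PROM-change correlation under Hypothesis 2.2. The direction follows from the stopping rule if surgery relieves pain. The size does not follow from the documents: under assumed inputs it runs from negligible to large. The pain limit protects patients and is not the error.

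This is a cheap improvement to one of two measures of a secondary endpoint. The primary endpoints and sample size do not depend on it. It is worth making because the information cannot be recovered later.

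**What to change.** In section 3.3, at both visits, record why the hold ended (muscle exhaustion, back pain, leg pain, other) and a 0-10 pain rating just before the hold and at its end. Report the stopwatch result as hold time, and claim less muscle fatigue only when the EMG parameter agrees.

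Keep every hold in the main analysis, without dropping or censoring pain stops. Add a sensitivity analysis by stop reason, labelled as a comparison of selected patients; this can sit in the statistical analysis plan. If a pain-adjusted version is wanted, adjust for pain before the hold. Pain at the stop should be descriptive only, because a longer hold can itself raise it and adjusting would condition on a consequence of the outcome.

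The cost is two or three form fields, a few sentences and a little extra analysis. The limitation is that patients may not cleanly separate pain from exhaustion, so the bias is reduced and made visible, not removed exactly.
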